## Abstract

**Introduction:**

Post-stroke spasticity affects 25%−40% of survivors, causing pain and functional impairment. Current non-invasive treatments target either central or peripheral pathways alone. This neglects the critical imbalance between spastic agonists and antagonists. We designed this protocol to address this gap through dual-site peripheral theta-burst stimulation.

**Methods:**

This single-center, three-arm, sham-controlled, single-blind randomized controlled trial enrolled 54 stroke survivors (aged 40–80, 3–12 months post-stroke, Modified Ashworth Scale score ≥1). Participants were randomized in a 1:1:1 ratio to receive a 10-session intervention over 2 weeks (5 days/week). Each session consisted of stimulation followed by 30 min of conventional physical therapy. The stimulation protocols were: Group 1: active iTBS over extensor carpi radialis longus + sham cTBS over flexor carpi radialis; Group 2: sham iTBS + active cTBS; Group 3: active iTBS + active cTBS. Stimulation was delivered using a MagTD stimulator at 110%−120% of the peripheral motor threshold (mean 38.4% maximum stimulator output), with 600 pulses per session (50 Hz burst frequency, 5 Hz theta rhythm).

**Anticipated results:**

We hypothesize that Group 3 (combined stimulation) will yield the greatest reduction in spasticity (MAS decrease ≥ 1) and the most significant improvements in upper-limb function (FMA-UE, ARAT) compared to Groups 1 and 2. These clinical gains are expected to correlate with neurophysiological changes (MEP amplitude, cortical silent period), supporting the central-peripheral synergy model.

**Discussion:**

This protocol tests a novel dual-site pTBS paradigm. Positive findings would provide preliminary evidence for network-based rehabilitation. This could inform larger trials and potentially transform post-stroke spasticity management.

## Introduction

Spasticity, a common yet not obligatory feature of upper motor neuron syndrome, often accompanies other sensorimotor deficits after central nervous system injury (1). Epidemiological data indicate that post-stroke spasticity occurred in 25.3% of all survivors, 26.7% of first-ever cases, and 39.5% when paresis was present. Among paretic patients, 9.4% had disabling/severe spasticity (Modified Ashworth Scale, MAS > 3) and 10.3% had severe spasticity (2). Clinically, spasticity is a key contributor to pain, joint contractures, impaired volitional movement, caregiver burden, and diminished quality of life (3). Although they are widely used, early rehabilitation, oral antispastic drugs, botulinum-toxin injections, and surgical decompression often confer only transient benefits and carry risks of systemic adverse effects or invasive complications (4–7). This underscores the critical demand for a non-invasive, precisely targeted, and sustainable neuromodulatory strategy to address post-stroke spasticity.

In recent years, central neuromodulation techniques—most notably repetitive transcranial magnetic stimulation (rTMS)—have shown promise in modulating cortical excitability and promoting neuroplasticity (8). Among these, theta burst stimulation (TBS) has garnered particular attention due to its time efficiency and polarity-specific effects:intermittent TBS (iTBS) facilitates cortical excitability, whereas continuous TBS (cTBS) exerts inhibitory effects (9). However, the majority of existing TBS studies have focused exclusively on the contralesional primary motor cortex (M1), with limited direct impact on peripheral spastic musculature. Although some studies have reported that central TBS can improve global upper-limb function, systematic reviews have noted that significant reductions in spasticity have not been consistently observed, with inconsistencies largely attributable to heterogeneity in stimulation parameters across studies (10). Therefore, current evidence suggests that targeting a single central site may be insufficient to address the multifactorial pathophysiology underlying post-stroke spasticity, which involves maladaptive remodeling across the cortex-spinal cord-muscle axis.

Repetitive peripheral magnetic stimulation (rPMS) delivers pulsed magnetic fields to peripheral nerves and muscles and is increasingly used for post-stroke upper-limb rehabilitation. Among various rPMS protocols, the theta-burst stimulation pattern—hereafter referred to as peripheral theta-burst stimulation (pTBS)—offers short-duration, polarity-specific plasticity induction. Among rPMS patterns, pTBS (including intermittent iTBS and continuous cTBS bursts) offers short-duration, polarity-specific plasticity induction. Hereafter we use pTBS to denote the rPMS protocol employed in this trial. By inducing afferent volleys and modulating synaptic plasticity at both spinal and cortical levels, pTBS may facilitate sensorimotor recovery (11). A recent systematic review indicated that pTBS exerts positive effects on muscle strength, spasticity, and functional impairment in stroke survivors (3). Nonetheless, existing studies have primarily targeted spastic muscles in isolation, yielding inconsistent outcomes in terms of muscle tone, passive range of motion, and voluntary control. These inconsistencies are largely attributable to heterogeneity in stimulation parameters (e.g., frequency, intensity, duration) and methodological differences in outcome assessment (12). More importantly, these investigations have largely overlooked the synergistic imbalance between spastic agonists and their antagonists and have not systematically explored a bidirectional central-peripheral network modulation strategy.

In recent years, our understanding of neuromodulatory mechanisms has continued to evolve. The “W-shaped” nonlinear model, originating from research on cognitive aging, posits that the relationship between cortical excitability and neural function is not linear (13). This model asserts that both excessively high and low states of cortical excitability are maladaptive, leading to impaired behavioral performance, while optimal cognitive function corresponds to an intermediate “optimal functional zone.” Although this model was developed in the cognitive domain, the core principle it reveals—the “excitability-function relationship” —likely represents a universal operating principle for neural networks. This is corroborated by the work of Buss et al., (14) which demonstrated that in cognitively healthy older adults, higher cognitive reserve is associated with lower motor cortex excitability. This suggests that a more optimized, moderate level of excitability forms the foundation for efficient neural processing. Critically, this principle provides a novel, integrative lens through which to understand post-stroke motor dysfunction. The classic post-stroke imbalance between hemispheres—characterized by hypoexcitability in the affected motor cortex and hyperexcitability in the unaffected hemisphere—precisely mirrors the two dysfunctional states at the extremes of the “W-shaped” model. Therefore, synergistically driving motor cortical excitability toward the central “optimal functional zone,” rather than merely applying unidirectional facilitation or inhibition, should constitute a more effective regulatory strategy. However, existing pTBS protocols have yet to leverage this theoretical framework. They typically lack a bidirectional design capable of simultaneously driving both hyper- and hypo-excitable neural circuits toward the “optimal functional zone” in an agonist-antagonist manner.

Building on this framework, we designed an RCT to formally test these mechanisms and establish clinical feasibility. This protocol makes three contributions: (1) a standardized PMT titration method, (2) first RCT testing the W-shaped model through dual-site pTBS, and (3) a rigorous sham-controlled design. Primary objectives are to evaluate pTBS effects on spasticity/function, investigate neurophysiological mechanisms, and establish safety profiles. Secondary objectives include validating central-peripheral synergy, comparing single vs. dual-site stimulation, and generating effect sizes for future trials.

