## Methods

### Study design

The study is a prospective, single-center, randomized, parallel-controlled design. Fifty-four patients will be randomly assigned to one of three groups (Figure 1): (1) active iTBS+sham cTBS; (2) sham iTBS+active cTBS; (3) active iTBS+active cTBS in 1:1:1 ratio. The trial comprises three phases (Table 1): baseline assessment, post-training assessment (i.e., after 10 sessions) and follow-up assessment (i.e., 2 weeks after the completion of all training sessions). Intervention will be conducted five sessions a week, with a total of 10 sessions. All participants will sign an informed consent form. Adverse reactions will be handled in accordance with the preset protocol. The whole study will be performed at the Department of Rehabilitation Medicine of South China Hospital of Shenzhen University (Shenzhen, Guangdong Province, China). The results will be published in peer-reviewed journals and reported at academic conferences. The protocol is registered with Chinese Clinical Trial Registry (Registration No. ChiCTR2500105190). The trial will be conducted in accordance with the Consolidated Standards of Reporting Trials (CONSORT) guidelines, and the study protocol has been approved by the Institutional Review Board of Ethics Committee of South China Hospital of Shenzhen University (grant no. HNL.S2025041).

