The iTBS protocol was configured to deliver a total of 600 pulses, organized into 20 trains. Each train consisted of 10 bursts, with an 8-s inter-train interval. Within each burst, three pulses were administered at a frequency of 50 Hz, and the bursts themselves were repeated at a theta frequency of 5 Hz. The total stimulation duration for the iTBS protocol was 200 s (Table 3). During treatment, participants will lie supine. For iTBS: the figure-of-eight double coil will be centered over the antagonist muscle—specifically, the most prominent belly of the extensor carpi radialis longus (ECRL), located 4 cm distal to the lateral epicondyle of the humerus and 1 cm radially (Figure 2). This location was confirmed through anatomical palpation and is standardized to ensure consistent targeting of the ECRL muscle belly, a common motor point for effective stimulation (20, 21). The coil plane will be flush with the skin surface, the handle oriented proximally and angled aligned parallel to the long axis of the forearm. The cTBS protocol was configured to deliver a total of 600 pulses in a single, continuous train of 200 bursts without interruption. The total stimulation duration for cTBS was 40 s, during which bursts were delivered continuously at a theta frequency of 5 Hz. Each burst contained three pulses administered at a frequency of 50 Hz. For cTBS: the coil will be centered over the spastic muscle—the most prominent belly of the flexor carpi radialis (FCR), located 5 cm distal to the medial epicondyle of the humerus and 1 cm ulnarly. Similarly, this site was determined based on anatomical landmarks to reliably target the FCR belly, promoting reproducible stimulation across sessions (20, 21). The coil plane will again lie flat against the skin, with the handle oriented proximally and aligned parallel to the long axis of the forearm. The stimulation intensity for both iTBS and cTBS was set at 110%−120% of the individual's peripheral motor threshold (PMT).

**Table 3 T3:** Detailed parameters for the peripheral theta-burst stimulation protocols.

**Parameter**	**iTBS**	**cTBS**
Total stimulation duration	200 s	40 s
Total pulses	600	600
Pulse frequency (within burst)	50 Hz	50 Hz
Pulses per burst	3	3
Burst frequency	5 Hz	5 Hz
Bursts per train	10	200
Total trains	20	1
Inter-train interval	8 s	N/A
Stimulation intensity	110%−120% of PMT	110%−120% of PMT

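### With no sham iTBS + sham cTBS arm, the trial can test whether dual-site beats single-site stimulation, but cannot validate synergy or estimate pTBS against no active pTBS

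*Protocol article*

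**What the plan says.** The Introduction of the protocol article sets out the aims. "Primary objectives are to evaluate pTBS effects on spasticity/function" comes first, and then: "Secondary objectives include validating central-peripheral synergy, comparing single vs. dual-site stimulation, and generating effect sizes for future trials". The same paragraph lists "a rigorous sham-controlled design" among the trial's contributions.

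Methods, Study design, gives the arms as "1) active iTBS+sham cTBS; (2) sham iTBS+active cTBS; (3) active iTBS+active cTBS in 1:1:1 ratio". The Abstract, the stimulation section and the legend of Figure 3 give the same three. Every participant also receives 30 minutes of conventional physical therapy (CPT) after stimulation. No arm is sham + sham or CPT alone.

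The Abstract (Anticipated results) expects Group 3 to do best "compared to Groups 1 and 2" on spasticity and upper-limb function. It expects these gains to correlate with neurophysiological change, "supporting the central-peripheral synergy model". The Statistical analysis section plans repeated-measures comparisons within groups, t-tests between groups, and a Spearman correlation of change in MEP amplitude (or cortical silent period) with change in FMA-UE.

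**The concern.** Two of the stated objectives ask for quantities that the randomised comparisons do not contain. To separate synergy from the sum of two effects, one must know what each site does alone relative to neither. To estimate the effect of pTBS as such, one needs a group without active pTBS. The article defines pTBS as covering both iTBS and cTBS, so every arm receives it.

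At stake is what a positive result may be called. If Group 3 wins, the wording invites the conclusion that synergy has been validated. If all arms improve, the within-group tests and the threshold of at least one MAS point invite the conclusion that pTBS works. Neither conclusion would rest on a randomised contrast.

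**Working it through.** **Inputs.** Arms: Study design. Pulses: stimulation section and Table 3. Sessions: 10 (Study design). The article gives no figure for synergy to reproduce; the only figures of its own used here are the pulse counts in step 5.

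**1. Model.** Let I = 1 if iTBS is active and C = 1 if cTBS is active. Write the arm mean as m + a·I + b·C + c·I·C, where c is the interaction.

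- G1 = m + a
- G2 = m + b
- G3 = m + a + b + c
- G0 (double sham, not randomised) = m

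The three randomised rows have rank 3 for four parameters.

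**2. What can be estimated.**

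- G3 - G1 = b + c: active cTBS against sham cTBS, given active iTBS.
- G3 - G2 = a + c: active iTBS against sham iTBS, given active cTBS.
- G2 - G1 = b - a.

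**3. What cannot.** Take weights w1, w2, w3 on the three arm means. To estimate c alone, the coefficient of c requires w3 = 1, that of a requires w1 + w3 = 0, and that of b requires w2 + w3 = 0. So w1 = w2 = -1. The coefficient of m is then -1 - 1 + 1 = -1, but it has to be 0, so no such estimator exists. The same check fails for:

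- iTBS alone against sham: w1 = 1, w2 = w3 = 0, leaving m with coefficient 1.
- cTBS alone against sham: w2 = 1 and the others 0, again leaving m.
- Dual stimulation against sham: w3 = 1 and the others 0, again leaving m.

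A larger sample does not change this.

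**4. Illustration (assumed values, not from the article).** Suppose the mean MAS changes are G1 = -0.5, G2 = -0.5 and G3 = -1.0. Both estimable contrasts are then -0.5. The interaction is c = G3 - G1 - G2 + G0 = -1.0 + 0.5 + 0.5 + G0 = G0, and G0 is unknown:

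| Assumed G0 | a = b | c | Reading |
|---|---|---|---|
| +0.25 | -0.75 | +0.25 | less than additive |
| 0 | -0.5 | 0 | exactly additive |
| -0.25 | -0.25 | -0.25 | partly synergistic |
| -0.5 | 0 | -0.5 | neither site works alone; all interaction |

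The same trial result fits all four rows. The planned correlation does not choose between them, because two additive effects on both neurophysiology and function would also make the change scores correlate.

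**5. Active stimulation per arm.** "The iTBS protocol was configured to deliver a total of 600 pulses, organized into 20 trains": 20 trains x 10 bursts x 3 pulses = 600, as stated. cTBS: 200 bursts x 3 pulses = 600, as stated. Groups 1 and 2 therefore receive 600 active pulses per session (6,000 over 10 sessions), and Group 3 receives 600 + 600 = 1,200 (12,000 over 10 sessions). The Abstract gives 600 pulses per session without splitting by group, and the Discussion sets a 600-pulse protocol against a cited maximum of 800 per session. These statements and Table 3 must be reconciled; the estimability result does not depend on how.

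**6. What a fourth arm would buy.** Adding G0 raises the rank to 4. The standard error of the interaction is 2 SD/√n per arm: 0.52 SD at n = 15 and 0.47 SD at n = 18. With 80% power at two-sided 5%, the detectable interaction is (1.960 + 0.842) times that, or 1.45 SD and 1.32 SD. A fourth arm at the present size (4 x 18 = 72 recruited) would therefore make the interaction estimable, but only a very large one detectable.

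**The case against.** **Synergy is not defined as an interaction.** The article never equates the two. Both stimuli are peripheral, so central-peripheral synergy need not mean iTBS x cTBS, and its support is said to come partly from a correlation. This stands as a point about terminology. But the basis offered, Group 3 best plus a correlation, still does not separate synergy from two effects that add.

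**Additivity need not predict a double win.** In the pilot described in the Discussion (n = 12), cTBS alone lowered MAS without improving ARAT, and iTBS alone did the reverse. With a = 0 on MAS, additivity gives G3 - G2 = a = 0, so Group 3 would only match Group 2 there, and by the same argument would match Group 1 on ARAT. This stands: additivity explains a win over both arms on one outcome only if both components act on that outcome. Yet reading such a win as interaction requires a = 0, which this trial cannot check. Under the pilot pattern Group 3 would also be best or joint best on both scales with no interaction on either.

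**The trial is sham-controlled.** A reader might infer that the label is wrong, or that the trial can give no evidence of pTBS efficacy. The documents do not support that. G3 - G1 and G3 - G2 are randomised comparisons with sham for the added component, and a positive one is evidence that the component works on top of the other.

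**Double the pulses is what dual-site means.** This is correct. The dose per site is constant at 600, as an add-on comparison needs, and the pulses go to different muscles. Total stimulation is therefore a limit on interpreting a win as synergy, not a flaw in the single-site versus dual-site comparison.

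**Conclusion.** The point holds for two claims: validating synergy, and the effect of pTBS read as pTBS against no active pTBS. Neither can be estimated from these arms at any sample size, because three means leave one of four parameters free. This rests only on the arms as stated and on reading synergy as something more than additive effects. The MAS values in the illustration are assumptions.

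The hypothesised comparison of Group 3 with Groups 1 and 2, and the objective of comparing single-site with dual-site stimulation, can both be estimated. Within-arm change cannot fill the gap. All arms receive active stimulation and CPT at 3–12 months after stroke, so such change mixes pTBS with therapy, natural recovery and placebo response. The defect lies in the stated objectives and the conclusions they permit, not in the randomised comparisons.

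**What to change.** 1. State the efficacy objectives as two contrasts: G3 - G1 (active cTBS added to active iTBS) and G3 - G2 (active iTBS added to active cTBS).
2. Keep the primary objective on pTBS effects, but qualify it as the effect of each component given the other.
3. Replace the synergy objective with a test of whether dual-site is superior to single-site stimulation, and remove "supporting the central-peripheral synergy model" from the Abstract.
4. Say that the trial cannot distinguish synergy from additivity or from greater total active stimulation.
5. Say that within-arm change, including the within-group tests and a MAS fall of at least one point, is descriptive and not evidence of efficacy.
6. Keep the sham-controlled label, described as component-wise.

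The cost is rewording and narrower claims. No new arm is required. If the sponsor wants to keep a synergy claim, a double-sham arm is the design that would identify it, and it would need its own sample-size justification.

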## Methods

### Study design

The study is a prospective, single-center, randomized, parallel-controlled design. Fifty-four patients will be randomly assigned to one of three groups (Figure 1): (1) active iTBS+sham cTBS; (2) sham iTBS+active cTBS; (3) active iTBS+active cTBS in 1:1:1 ratio. The trial comprises three phases (Table 1): baseline assessment, post-training assessment (i.e., after 10 sessions) and follow-up assessment (i.e., 2 weeks after the completion of all training sessions). Intervention will be conducted five sessions a week, with a total of 10 sessions. All participants will sign an informed consent form. Adverse reactions will be handled in accordance with the preset protocol. The whole study will be performed at the Department of Rehabilitation Medicine of South China Hospital of Shenzhen University (Shenzhen, Guangdong Province, China). The results will be published in peer-reviewed journals and reported at academic conferences. The protocol is registered with Chinese Clinical Trial Registry (Registration No. ChiCTR2500105190). The trial will be conducted in accordance with the Consolidated Standards of Reporting Trials (CONSORT) guidelines, and the study protocol has been approved by the Institutional Review Board of Ethics Committee of South China Hospital of Shenzhen University (grant no. HNL.S2025041).

**Figure 1 F1:**
[figure not shown]
Flowchart of the proposed randomized controlled trial. Group 1: Active iTBS + sham cTBS combined with CPT; Group 2: sham iTBS + active cTBS combined with CPT; Group 3: Active iTBS + active cTBS combined with CPT. CPT, conventional physical therapy; FMA-UE, Fugl-Meyer assessment for upper extremity.

**Table 1 T1:** Schedule of participant recruitment, intervention and assessments.

**Time point**	**–T1**	**T0**	**T1**	**T2**
Recruitment	√			
Eligibility screening	√			
Informed consent	√			
Randomization		√		
**Intervention**
Group 1		√	√	√
Group 2		√	√	√
Group 3		√	√	√
**Assessment**
MEPs	√	√	√	√
MAS	√	√	√	√
FMA-UE		√	√	√
ARAT		√	√	√
Modified Barthel index		√	√	√

– T1, screening; T0, baseline; T1, post-intervention; T2, 2-week follow-up; MEPs, motor-evoked potentials; MAS, Modified Ashworth Scale; ARAT, action research arm test.

### Sample size estimation

As the differential effects of priming iTBS on hemiparetic upper-limb training have yet to be examined, we based our sample-size estimate on existing three-group trials. A recent meta-analysis reported a pooled Cohen's *d* = 0.60 favoring iTBS for upper-limb motor improvement. For a three-group design, this translates to an effect size *f* of ~0.30 (15). *A priori* power analysis (power = 0.80, two-tailed α = 0.05) indicated that 45 participants would be required. Accounting for an anticipated 15% dropout rate, we will recruit 18 participants per group, for a total sample size of 54. This recruitment target is expected to yield at least 45 participants completing the trial.

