### Theta burst stimulation protocol targeting antagonist and spastic muscles

The flexor carpi radialis (FCR) and extensor carpi radialis longus (ECRL) were selected as stimulation targets based on their established role as a primary agonist-antagonist pair responsible for the wrist flexion-extension imbalance in post-stroke upper limb spasticity. The central mechanistic hypothesis is that the spatial proximity of their cortical representations within the primary motor cortex enables the simultaneous modulation of this pair to preferentially target a shared cortical microcircuit, thereby regulating its excitatory-inhibitory balance to reset abnormal motor output (16).

All enrolled participants will receive iTBS, cTBS or sham stimulation before CPT session each weekday, Group 1: active iTBS to the antagonist plus sham cTBS to the spastic muscle. Group 2: sham iTBS to the antagonist plus active cTBS to the spastic muscle. Group 3: active iTBS to the antagonist plus active cTBS to the spastic muscle (Figure 2). The intervention will last for two consecutive weeks, with all procedures strictly adhering to the 2021 safety guidelines issued by the International Federation of Clinical Neurophysiology (17). Stimulation will be delivered with a MagTD transcranial magnetic stimulator (MagTD; Wuhan Yiruide Medical Device Technology Co., Ltd., Wuhan, China) and a figure-of-eight double coil (maximum field strength = 2 T, diameter = 9 cm). The coil center will be placed tangentially over the target muscle group, with the induced current directed downward. For the sham stimulations, we choose the Magstim's70 mm figure-of-eight double rapid2 air cooled coil (P/N 3910-00 S/NO 728) (18). The coils were identical in external appearance which ensured that the patients remained blind to the intervention (Figure 3).

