## Discussion

The W-shaped excitability framework—where both hyper- and hypo-excitability impair function—doesn't map neatly onto post-stroke spasticity (28). Stroke does not produce a uniform excitability shift; it may create a spatially dissociated pathology characterized by spinal hyperexcitability in spastic flexors and, as suggested by our pilot data and others, cortical hypo-excitability in their antagonists; accordingly, this “split-modulation” approach emerged from pilot data (*n* = 12) where cTBS alone reduced MAS scores without improving ARAT, and iTBS alone did the opposite—suggesting that resetting the network requires both levers (28).

Parameter selection bypassed convention in favor of peripheral nerve physiology. The 110%−120% PMT intensity—averaging 38.4% MSO in our pilot—produced a 15%−20% increase in M-wave amplitude, the narrow band where Ia fibers activate without recruiting nociceptive afferents (20). Below this threshold, spinal plasticity markers (H-reflex suppression) vanished on TMS-EEG (27); above it, tolerance dropped below 70% within 15 min. The 600-pulse dose was selected based on a balance between efficacy and safety. The IFCN guidelines recommend a maximum of 800 pulses per session for peripheral TBS protocols to ensure safety (17). Furthermore, doses of 400–800 pulses have been commonly employed in prior rPMS studies and are considered necessary to induce consistent neurophysiological changes at the spinal level, such as H-reflex suppression (11, 21). Thus, our 600-pulse protocol operates within established safety boundaries while aligning with doses used in effective rPMS studies.

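### The 80% power statement rests on an iTBS motor effect, so it does not cover Group 3 vs Group 1 (both receive active iTBS) or any MAS comparison

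*Protocol article*

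**What the plan says.** Sample size estimation gives one source for the effect: "A recent meta-analysis reported a pooled Cohen's *d* = 0.60 favoring iTBS for upper-limb motor improvement". It continues: "For a three-group design, this translates to an effect size *f* of ~0.30 (15"). The "power analysis (power = 0.80, two-tailed α = 0.05) indicated that 45 participants would be required", and then: "Accounting for an anticipated 15% dropout rate, we will recruit 18 participants per group, for a total sample size of 54". This is the article's only power statement.

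Study design lists the arms as ("1) active iTBS+sham cTBS; (2) sham iTBS+active cTBS; (3) active iTBS+active cTBS in 1:1:1 ratio". The section on the theta burst protocol repeats the allocation by muscle, for example "Group 1: active iTBS to the antagonist plus sham cTBS to the spastic muscle". Groups 1 and 3 therefore receive the same active iTBS and differ only in whether cTBS is active or sham.

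The hypothesis is in the abstract under Anticipated results: "Group 3 (combined stimulation) will yield the greatest reduction in spasticity (MAS decrease ≥ 1"), together with the largest gains on FMA-UE and ARAT, relative to both other groups. The last paragraph of the Introduction places spasticity and function together among the primary objectives.

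**The concern.** The plan hypothesises superiority of Group 3 over each of two comparators on three outcomes, and supports this with a power figure built from one effect on one kind of outcome.

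Two mismatches follow, for different reasons. In Group 3 vs Group 1 the iTBS component is common to both arms, so an effect of iTBS against no iTBS does not describe the difference. For MAS, the borrowed effect concerns motor improvement, so it describes no spasticity contrast, whichever arms are compared.

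At stake is how the results are read. A reader who takes the 80% at face value may treat a non-significant Group 3 vs Group 1 result, or a non-significant MAS result, as an adequately powered negative. The document gives no basis for that.

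**Working it through.** **The plan's own figure.** Inputs from Sample size estimation: f = 0.30, three groups, α = 0.05, power 0.80, N = 45.
- f = d/2 = 0.60/2 = 0.30, which is the two-group conversion.
- One-way ANOVA, noncentrality λ = N·f². At N = 45, λ = 45 × 0.09 = 4.05 and power is 39.4%. At N = 54, λ = 4.86 and power is 46.8%. Reaching 80% needs N = 111 (37 per arm).
- The 45 is therefore not reproduced by a between-group test. It appears only with unstated inputs, such as a group-by-time interaction with two time points and a correlation near 0.25.
- Dropout: 45/0.85 = 52.9, so 53, which is consistent with 54 in equal arms; 54 × 0.85 = 45.9.

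The failure of 45 to follow from f = 0.30 is a separate defect. The point below would remain if N were corrected.

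**What each contrast estimates.** Let i be the effect of iTBS alone, c the effect of cTBS alone, and x any interaction (synergy), all measured from a common both-sham level that no arm observes.

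| Arm | Mean above that level |
|---|---|
| Group 1 | i |
| Group 2 | c |
| Group 3 | i + c + x |

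- Group 3 − Group 1 = c + x. The term i drops out, with or without additivity.
- Group 3 − Group 2 = i + x.

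If d = 0.60 is iTBS against sham or no iTBS (an assumption), it informs i, and so informs in kind only Group 3 − Group 2 on motor outcomes. The article gives no value for c, for x, or for any of these terms on MAS.

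**What the planned numbers can detect.** Statistical analysis names the independent-samples t-test for between-group comparison of normal data. Two-sided 5% test, noncentrality d·√(n/2), 2n − 2 degrees of freedom:

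| Completers per arm | Power, d = 0.3 | d = 0.5 | d = 0.6 | Detectable d at 80% |
|---|---|---|---|---|
| 15 | 12.5% | 26.2% | 35.5% | 1.06 |
| 18 | 14.1% | 30.8% | 41.7% | 0.96 |

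The values 0.3 and 0.5 are assumed, to show a range. For d = 0.6 the noncentralities are 0.6 × √7.5 = 1.64 and 0.6 × √9 = 1.80. These figures reflect the small arms and would be the same for a perfectly matched effect size. They show what the design can detect; they do not measure the mismatch.

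With baseline adjustment at an assumed correlation ρ, the detectable difference shrinks by about √(1 − ρ²). At 15 per arm this gives 1.06 × 0.866 = 0.92 SD for ρ = 0.5 and 1.06 × 0.714 = 0.76 SD for ρ = 0.7.

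**Isolating the mismatch.** Take 45 per arm, where d = 0.60 does give 80% (this is not the protocol's design). If the effect of active cTBS on top of iTBS, c + x, were 0.2 or 0.3 SD (assumed), power for Group 3 vs Group 1 would be 15.5% or 29.1%. A sample large enough for the iTBS effect gives no assurance for the cTBS contrast.

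**MAS.** No power can be computed, because the article gives no MAS effect size, SD or responder rate.

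**The case against.** The strongest reply is that the article attaches its 80% to a three-group effect size f and never claims it for Group 3 vs Group 1 or for MAS. That is correct, and so there is no such sentence to delete. But it is the only power statement, and an omnibus rejection could come entirely from Group 2 lying lower. It does not support the pairwise claims in the abstract, and the scope needs to be stated.

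A reader might infer that the effect size fits none of the hypothesised comparisons. The documents do not support that: Group 3 vs Group 2 is active against sham iTBS, and d = 0.60 fits it in kind for motor function.

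A reader might also take the pilot remark in the Discussion, "cTBS alone reduced MAS scores without improving ARAT, and iTBS alone did the opposite", as showing that the expected difference is zero for ARAT against Group 1 and for MAS against Group 2, and that Group 3 has almost no chance of beating both. That goes too far. The pilot had 12 patients, no estimates are given, and FMA-UE is not mentioned. A zero difference also requires additive effects, while the trial hypothesises synergy (x above zero). Joint success probabilities from an additive model assume that hypothesis away. What stands is narrower: the pilot remark gives no reason to let an iTBS motor effect stand in for a cTBS effect or a spasticity effect.

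Finally, the article calls the evidence preliminary, concedes a modest sample, and lists effect sizes for future trials as an aim. That softens the consequence but does not alter what the power sentence covers.

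**Conclusion.** The point holds in this limited form. The single power statement rests on an iTBS motor effect. It does not extend to Group 3 vs Group 1 on any outcome, or to MAS in any contrast, because the article gives no effect size for either. It fits in kind Group 3 vs Group 2 on motor function.

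The pairwise difference detectable with 80% power is about 1.06 SD at 15 completers per arm and 0.96 SD at 18, for one unadjusted two-sided 5% t-test; baseline adjustment lowers it. For MAS, an ordinal scale, these values are only indicative.

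The conclusion assumes that the unnamed comparator in the meta-analysis was sham or no iTBS. It does not depend on additivity or on the pilot. It concerns what the power figure supports; it does not show that the hypothesis or its contrasts are wrong. The correction should be made, but it calls for no change of design.

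**What to change.** In Sample size estimation:
- State that d = 0.60 informs only Group 3 vs Group 2 on motor function, and name the comparator behind it.
- State that the 80% figure does not extend to Group 3 vs Group 1 or to MAS.
- Give the detectable difference for a pairwise unadjusted two-sided 5% t-test: about 1.06 SD at 15 completers per arm and 0.96 SD at 18, noting that baseline adjustment would reduce it.

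Report Group 3 vs Group 1 and all MAS contrasts as estimates with confidence intervals, and say in advance that a non-significant result there will not be read as evidence against dual-site stimulation.

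Keep the hypothesis in the abstract and its contrasts. Assigning each outcome to a single contrast would give up the trial's own question of single against dual-site stimulation.

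The cost is wording, with no extra patients, visits or procedures. The downside is a less favourable power statement. The derivation of 45 from f = 0.30 has to be corrected separately.
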